# Compensatory changes in energy balance during dapagliflozin treatment in type 2 diabetes mellitus: a randomised double-blind, placebo-controlled, cross-over trial (ENERGIZE)—study protocol

**DOI:** 10.1136/bmjopen-2016-013539

**Published:** 2017-01-27

## Abstract

**Introduction:**

Sodium glucose cotransporter 2 (SGLT2) inhibitors are effective blood-glucose-lowering medications with beneficial effects on body weight in patients with type 2 diabetes mellitus (T2DM). However, observed weight loss is less than that predicted from quantified glycosuria, suggesting a compensatory increase in energy intake or a decrease in energy expenditure. Studies using dual-energy X-ray absorptiometry (DEXA) have suggested most body weight change is due to loss of adipose tissue, but organ-specific changes in fat content (eg, liver, skeletal muscle) have not been determined. In this randomised, double-blind, placebo-controlled crossover study, we aim to study the compensatory changes in energy intake, eating behaviour and energy expenditure accompanying use of the SGLT2 inhibitor, dapagliflozin. Additionally, we aim to quantify changes in fat distribution using MRI, in liver fat using proton magnetic resonance spectroscopy (^1^H-MRS) and in central nervous system (CNS) responses to food images using blood oxygen level dependent (BOLD) functional MRI (fMRI).

**Methods and analysis:**

This outpatient study will evaluate the effect of dapagliflozin (10 mg), compared with placebo, on food intake and energy expenditure at 7 days and 12 weeks. 52 patients with T2DM will be randomised to dapagliflozin or placebo for short-term and long-term trial interventions in a within participants, crossover design. The primary outcome is the difference in energy intake during a test meal between dapagliflozin and placebo. Intake data are collected automatically using a customised programme operating a universal eating monitor (UEM). Secondary outcomes include (1) measures of appetite regulation including rate of eating, satiety quotient, appetite ratings (between and within meals), changes in CNS responses to food images measured using BOLD-fMRI, (2) measures of energy expenditure and (3) changes in body composition including changes in liver fat and abdominal visceral adipose tissue (VAT) and subcutaneous adipose tissue (SAT).

**Ethical approval:**

This study has been approved by the North West Liverpool Central Research Ethics Committee (14/NW/0340) and is conducted in accordance with the Declaration of Helsinki and the Good Clinical Practice (GCP).

**Trial registration number:**

ISRCTN14818531. EUDRACT number 2013-004264-60.

Strengths and limitations of this studyThis is the first study to address the discrepancy between the estimated and actual weight loss as a result of SGLT2 inhibition in a prospective within participant study design incorporating short-term and long-term effects.The study is designed to assess macrostructure and microstructure of eating behaviour and the use of imaging modalities provide a neurophysiological and mechanical correlate.The sample size is relatively small, although provides sufficient power to answer the primary research question.The measurement of energy expenditure is performed using indirect calorimetry as opposed to the gold standard whole body calorimetry.There may be a carryover effect on body weight and body composition changes since there is no wash-out period between the long-term cross over, but any effect of this on the primary outcome (food intake) should be minimal.

## Background and rationale

Type 2 diabetes mellitus (T2DM) is a disorder characterised by hyperglycaemia and insulin resistance, which leads to the development of microvascular and macrovascular complications. It is a major global public health challenge; the prevalence is expected to rise to 592 million by 2035.^1^ A range of pharmacological therapies to complement lifestyle interventions with diet and exercise are available including biguanides, sulphonylureas, thiazolidenediones, glucagon-like peptide-1 (GLP-1) agonists and dipeptidyl peptidase-IV (DPP-IV) inhibitors, as well as insulin. These therapies are usually unable to alter the natural progression of T2DM. Obesity is a major risk factor for T2DM, yet some treatments, particularly sulphonylureas, thiazolidenediones and insulin, may cause weight gain. Hence therapeutic agents that are weight neutral or associated with weight loss may be preferable. Inhibition of renal tubular reabsorption of glucose to induce glycosuria is effective in animal models^2^ and has led to the development of sodium/glucose cotransporter 2 (SGLT2) inhibitors for clinical use.

SGLT2 inhibitors such as dapagliflozin have been shown to cause significant reductions in glycaemia in patients with T2DM, comparable with those produced by other oral agents.^3–6^ In contrast to existing oral agents, treatment results in weight loss in all groups studied to date, including treatment-naive patients and those where SGLT2 inhibitors were added to other oral agents, insulin alone or a combination of oral agents with insulin. SGLT2 inhibition results in a net loss of ∼75 g glucose per day, equivalent to an energy loss of ∼300 kcal/day (1200 kJ/day), and also a diuresis (∼400 mL/day), resulting in a modest intravascular volume depletion (evidenced by a rise in haematocrit). The predicted weight loss over 24 weeks treatment with dapagliflozin (assuming no compensatory changes in either food intake or energy expenditure and no diuresis) based on the calculated caloric loss would be ∼7 kg. However, clinical data so far suggest that the observed total weight loss with dapagliflozin 10 mg dose is 2.5–3.2 kg (1.7–2.0 kg placebo-subtracted), that is, an actual (placebo-subtracted) energy deficit of ∼320 kJ/day, which is substantially less than the measured urinary energy losses.

This suggests that with chronic treatment there are compensatory mechanisms that attenuate weight loss.^7^ These could include either an increase in food intake, driven by hunger (weakened satiety) and increased responsiveness to food cues (reward driven wanting), or a reduction in energy expenditure. As in human T2DM, rats with dietary-induced obesity lose weight when treated with dapagliflozin (∼4%), but this is offset by a 30% compensatory increase in energy intake.^8^ Furthermore, pair-feeding matched to vehicle-treated animals leads to greater weight loss of ∼13%. In SGLT2 knockout mice, food intake was greater during the dark cycle than controls; physical activity also increased, energy expenditure was higher and respiratory quotient (RQ) fell, consistent with a shift from carbohydrate to fat metabolism. Human studies also demonstrate a shift from glucose to fat metabolism.^9^ Overall these data are consistent with the observations in humans and suggest that some compensatory increase in food intake occurs that limits the weight loss in dapagliflozin treatment; the metabolic changes also suggest that fuel usage may shift from carbohydrate to fat metabolism.^10^ Considering the associated weight loss, improved glycaemia and preference for fat metabolism, we believe that liver fat may also be reduced, an effect observed with GLP-1 receptor agonists.^11^

This study is designed to examine the behavioural and biological mechanisms underlying the changes in energy balance that occur with treatment with the SGLT2 inhibitor, dapagliflozin, to evaluate changes in body composition and also to help answer important physiological questions regarding adaptive responses to a state of negative energy balance mediated by promoting glycosuria.

## Primary objective

To evaluate the effect of dapagliflozin, 10 mg daily, compared with placebo, when added to up to two other oral glucose-lowering medications, on energy intake at a test meal after 12 weeks of oral administration of treatment.

## Secondary objectives

To evaluate the changes in the following outcome measures with dapagliflozin, 10 mg daily, after 7 days and at 12 weeks, compared with placebo, when added to up to two other oral glucose-lowering medications on:
Energy intake and appetite expression at a test meal after 7 days (hunger and satiety).Total energy expenditure and RQ derived from ventilated hood measurements after 7 days and after 12 weeks.Changes in central nervous system (CNS) responses to food images using blood oxygen level dependent (BOLD) fMRI after 7 days and after 12 weeks (reward driven eating).Visceral and subcutaneous adipose tissue volumes (VAT/SAT) using MRI after 12 weeks.Liver fat, using proton magnetic resonance spectroscopy (^1^H-MRS).

In addition, this study will address the effects of dapagliflozin on the rate of eating and satiety quotient.

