### Study visits and procedures

#### Test meal visits (visits 1, 3, 5, 9 and 13)

These will take place at baseline, after 7 days and 14 days, 14 weeks and 26 weeks of treatment (tables 1 and 2). On visit 1, participants will be asked to attend the investigational unit at 8:00, having had nothing to eat or drink other than water from midnight. To keep study procedures identical for all test days, participants will then be asked to take a dose of (single blind) placebo tablet. Participants will be weighed and their pulse and blood pressure recorded. An explanation and demonstration of Visual Analogue Scale (VAS) questionnaires, universal eating monitor (UEM) and ventilated hood will be given.

**Table 1 BMJOPEN2016013539TB1:** Study procedures

Time point guidelines	Procedure
Arrival 8:30	7 mL blood sample taken (visit 9 only)
	Placebo tablet taken
	Weight, pulse and blood pressure taken. Participants asked to empty bladder and start of timed urine collection
08:40	Basal metabolic rate measurement (indirect calorimetry—see below for details)
08:50	Participants will complete a series of pre-breakfast VAS ratings to measure hunger and other subjective variables
09:00	Participants will be provided with a fixed-quantity breakfast, consisting of cornflakes with milk, toast and preserve, tea/coffee and orange juice
10:00, 11:00, 12:00 (first one followed by 3 every hour)	Participants will complete the same set of VAS ratings as used pre-breakfast, providing a premeal set of ratings
10:00	Indirect calorimetry
11:00	Indirect calorimetry
12:00	Indirect calorimetry
13:00	Participants will be given a test meal in the UEM laboratory. The meal consists of a pasta dish with tomato sauce, and participants may eat ad lib and signal when they have finished the meal. The UEM will continuously monitor decreases in food as it is consumed and will provide a continuous record of food consumption throughout the meal
14:00, 15:00, 16:00, 17:00 (1st one followed by 3 every hour)	Participants will complete the same set of VAS ratings as used pre-breakfast, providing a postmeal set of ratings
14:00	Indirect calorimetry
15:00	Indirect calorimetry
16:00	Indirect calorimetry

UEM, universal eating monitor; VAS, Visual Analogue Scale.

**Table 2 BMJOPEN2016013539TB2:** Assessments and procedures during screening and study visits

Procedure	D −21 to −2	D 0	D 5–6	D 7	D 12–13	D 14	W 6	W 10	W 13–14	W 14	W 18	W 22	W 25–26	W 26
Visit	0	1	2	3	4	5	6	7	8	9	10	11	12	13

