##### Indirect calorimetry

Energy expenditure, resting metabolic rate (RMR) and RQ will be measured by indirect calorimetry data using a ventilated hood system and derived using the Weir equation.^14^
^15^ Measurements will be started after 5 min and performed for a 20 min period prior to the test meal and at 60, 120, 180 and 240 min postprandially. The first 5 min of each measurement will be discarded to allow for complete acclimatisation to the hood and the recumbent position, so that participants will have reclined for 10 min prior to any measurements being recorded for analysis. Urinary nitrogen excretion will be estimated by collecting all urine produced over the eight-hour period of observation in the laboratory and multiplying by a factor of 3 to approximate 24-hour urinary nitrogen excretion. Urine glucose excretion will also be measured over the same time period.

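### The hood outcome is labelled total energy expenditure although activity is not measured, its two schedules disagree, and the post-lunch sessions cannot separate lower expenditure from a larger meal

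*Protocol article*

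**What the plan says.** **Label.** Secondary objectives names "Total energy expenditure and RQ derived from ventilated hood measurements after 7 days and after 12 weeks". The abstract speaks only of measures of energy expenditure.

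**Method.** The Indirect calorimetry section states: "Energy expenditure, resting metabolic rate (RMR) and RQ will be measured by indirect calorimetry data using a ventilated hood system". Measurement begins after 5 minutes and is "performed for a 20 min period prior to the test meal and at 60, 120, 180 and 240 min postprandially". It adds: "The first 5 min of each measurement will be discarded to allow for complete acclimatisation to the hood and the recumbent position", so that 10 minutes of reclining precede any recorded data.

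**Timetable.** Table 1, whose time column is headed as guidelines, has arrival at 8:30. At 08:40 it places "Basal metabolic rate measurement (indirect calorimetry—see below for details", followed by appetite ratings at 08:50 and a fixed-quantity breakfast at 09:00. Hood sessions follow at 10:00, 11:00 and 12:00. The test meal is at 13:00, where "participants may eat ad lib and signal when they have finished the meal". Further hood sessions are at 14:00, 15:00 and 16:00, and appetite ratings continue to 17:00. The text above Table 1 asks for attendance at 8:00 on visit 1.

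**Related statements.** Energy intake at the 13:00 meal is the primary outcome (Abstract, Primary objective). The Strengths and limitations list concedes that indirect calorimetry is used in place of whole-body calorimetry.

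**The concern.** The Background asks whether weight loss on dapagliflozin is blunted by eating more or by spending less. The hood data are the article's only evidence on the second route.

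Three things weaken that evidence. A result reported as total expenditure would be read as covering physical activity, which the described measurements do not observe. Staff who follow the methods text and staff who follow Table 1 would collect different sessions. Finally, half of Table 1's postprandial sessions come after a meal whose size is itself expected to depend on treatment, so a difference there could come from metabolism or from the amount eaten.

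**Working it through.** The plan gives no sample size or expected effect for expenditure, so there is no expenditure figure to reproduce. The planned 52 concerns intake and does reproduce. The SD of the difference is 165 × √(2 × (1 − 0.7)) = 127.8 g. Against 57.5 g, a paired t-test at 80% power needs 41, and 41 / 0.8 = 51.25, rounded up to 52. Nothing below alters it.

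**1. What the sessions cover.** Inputs: 20 minutes per session, of which 5 are discarded (Indirect calorimetry); session counts from that section and from Table 1; an eight-hour laboratory stay (Indirect calorimetry).

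| Source | Sessions | Measured | Share of 24 h | Share of 8 h | Usable, if the 5 discarded min are part of the 20 |
|---|---|---|---|---|---|
| Indirect calorimetry text | 1 + 4 = 5 | 5 × 20 = 100 min | 100/1440 = 6.9% | 100/480 = 20.8% | 75 min (5.2% of 24 h) |
| Table 1 | 7 | 7 × 20 = 140 min | 140/1440 = 9.7% | 140/480 = 29.2% | 105 min (7.3% of 24 h) |

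All of this time is recumbent. The article describes no activity, free-living or 24-hour expenditure measure.

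**2. The two schedules.** The methods text wants readings at 60, 120, 180 and 240 minutes after a meal. Table 1's sessions, counted from each meal, fall as follows.

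| Counted from | Table 1 sessions (min) | Where 240 min falls |
|---|---|---|
| Breakfast, 09:00 | 60, 120, 180, 300, 360, 420 | 13:00, when the test meal is served |
| Test meal, 13:00 | 60, 120, 180 | 17:00, appetite ratings only |

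Neither meal gives a 240-minute session, and the counts differ (5 against 7).

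**3. The basal session.** There are two readings of the 08:40 entry.

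- Participant reclines at 08:40: 5 min of rest, measurement from 08:45 to 09:05, usable data from 08:50 to 09:05. It overlaps the 08:50 ratings and runs 5 min into the breakfast slot.
- Measurement starts at 08:40: it runs to 09:00, with usable data from 08:45 to 09:00. It overlaps the 08:50 ratings and leaves no slack before breakfast.

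**4. Sessions after the ad libitum meal.** In Table 1 these are 14:00, 15:00 and 16:00, or 3 of 6 postprandial sessions (50%). If the methods text counts from the test meal, all four of its postprandial readings follow it.

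For scale, assume an energy density of 1 to 2 kcal/g and a thermic effect of 5 to 15%. Neither value is in the documents.

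- Extra energy eaten for the planned 57.5 g difference: 57.5 × 1 = 57.5 kcal to 57.5 × 2 = 115 kcal.
- Extra expenditure: 57.5 × 0.05 = 2.9 kcal to 115 × 0.15 = 17.3 kcal.
- Expected spending in 3 h, from 1780 to 2100 kcal/day (Outcome measures): 1780 × 3/24 = 222.5 kcal to 2100 × 3/24 = 262.5 kcal.
- Ratio: 2.9/262.5 = 1.1% to 17.3/222.5 = 7.8%, if the whole thermic effect falls within the 3 h.

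**The case against.** The label can be defended. Secondary objectives ties the term to the hood in the same sentence, the article never says 24-hour or free-living, and *total* could mean the laboratory day. A condensed article may leave the definition to the full protocol, and the instrument limitation is disclosed. Part of this stands: the fault is in a label, not in the measurement. But the disclosure concerns the instrument and does not withdraw or define the word. Even over an eight-hour stay the sessions sample at most 29% of the time, all of it lying down. The methods text also triples eight-hour urinary nitrogen to approximate 24 hours. That makes a 24-hour reading natural, though it does not establish one.

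Three stronger conclusions might be inferred, and the documents do not support them.

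- *The fasting reading is spoiled at every visit.* Table 1's times are guidelines, and one reading of 08:40 finishes at 09:00. Nothing says a session is cut short or that breakfast is eaten during it. Appetite ratings also share the hour with hood sessions at 10:00, 11:00 and 12:00.
- *Post-lunch sessions contaminate the treatment comparison.* Nothing says they are pooled with the other sessions. The Analysis section fixes a model type, and how sessions are summarised can properly be left to an analysis plan. Expenditure after a freely chosen meal is also a valid total treatment effect.
- *Meal thermogenesis hides a fall in expenditure.* No expected fall is stated for comparison, and the 3 to 17 kcal rests on outside assumptions.

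The 240-minute conflict has no such answer. It is a disagreement between two stated schedules, and no choice of meal removes it.

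**Conclusion.** The point holds for the secondary expenditure and RQ outcomes.

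- **Firm on the text:** the sessions yield resting and postprandial expenditure, 100 to 140 minutes or 7 to 10% of a day (75 to 105 usable minutes, 5 to 7%), and are labelled total. The two schedules conflict on the number of sessions and on the 240-minute reading.
- **Needs adjusting:** the basal session overlaps the 08:50 ratings on either reading, with zero slack or a 5-minute overlap at breakfast. That is a timetable fault, not evidence of bad data.
- **Limit on interpretation:** the 14:00 to 16:00 sessions cannot separate a direct fall in expenditure from the thermic effect of a larger meal. The documents do not give the size; the 1 to 8% of three-hour expenditure is an illustration on assumed energy density and thermic effect.

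The correction is worth making because it sets what the trial may conclude about intake versus expenditure. The primary outcome and the 52 participants are untouched.

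**What to change.** 1. Rename the outcome *resting and postprandial energy expenditure (laboratory observation period)* and limit the conclusion to that.
2. Reconcile the Indirect calorimetry section with Table 1: the number of sessions, the meal they are counted from, and whether a 240-minute reading exists.
3. Reconcile the 8:00 and 8:30 arrival times, and time the basal session to finish before breakfast and clear of the 08:50 ratings.
4. Use fasting resting metabolic rate and the 10:00 to 12:00 sessions, which follow a fixed breakfast, for the direct comparison of expenditure and RQ. Report the 14:00 to 16:00 sessions separately, with the amount eaten, as a total treatment effect.

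The cost is mainly wording, a slightly narrower claim and possibly an earlier start to the visit. The fasting and post-breakfast sessions are already scheduled, and the eating monitor already records the amount eaten. A further session is needed only if the reconciliation keeps the 240-minute reading.

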## Methods and analysis

### Overall design, investigational plan and study population

This will be an outpatient, double-blind, placebo-controlled crossover study, to compare the effects of dapagliflozin with placebo on food intake and energy expenditure over periods of 7 days and 12 weeks. Fifty-two participants with T2DM will be recruited: aged 18–75 years, with glycated haemoglobin (HbA1c) <11% (97 mmol/mol) and either HbA1c ≥6.5% (48 mmol/mol) in patients who are not on sulphonylureas (eg, gliclazide, glimepiride), or HbA1c ≥7.0% (53 mmol/mol) in patients who are on sulphonylureas. Each participant will visit the study centre on 12 occasions: first, to undertake routine screening tests. If identified as eligible, subsequent visits involve consuming a test meal at baseline or following placebo or dapagliflozin 10 mg, respectively, and to undertake MR measurements. All patients will receive 7 days of dapagliflozin or placebo followed by 12 weeks of each treatment. Each participant will serve as their own control with the crossover between drug and placebo at short-term and long-term. The 7-day cross-over measurements will determine the short-term effects of energy loss on food intake and energy expenditure (at this stage, it is unlikely that significant weight loss would have occurred), while the long-term crossover at 12 weeks investigates the compensatory changes at dynamic stages of weight loss. The overall study design is illustrated (figure 1), with the full crossover design shown as study schematic (figure 2). Participants will be randomised to one of the four treatment sequences (figure 2).

**Figure 1 BMJOPEN2016013539F1:**
[figure not shown]
Study schematic.

**Figure 2 BMJOPEN2016013539F2:**
[figure not shown]
Study crossover schematic.

The inclusion and exclusion criteria for the study are summarised below.

### Inclusion criteria

T2DM, either treated with diet alone or up to two other oral agents (excluding pioglitazone) with an HbA1c ≥6.5% (48 mmol/mol) in patients who are not on sulphonylureas (eg, gliclazide, glimepiride) and ≥7.0% (53 mmol/mol) in those patients who are on sulphonylureas and <11% (97 mmol/mol).BMI 20–50 kg/m^2^.Men and women, age 18–75 years.

### Exclusion criteria

Medical history and concurrent diseases
Type 1 diabetes mellitus.History of diabetic ketoacidosis or hyperosmolar non-ketotic coma.Hyperthyroidism.Hypothyroidism (although participants with a normal TSH and free T4, and on a stable dose of thyroxine for at least 3 months, may be included).Uncontrolled hypertension (blood pressure >150/90 mm Hg).Recent (<6 months) myocardial infarction.Previous stroke.Significant cardiac dysrhythmias (including pacemaker or implantable cardiac defibrillator device).Known liver cirrhosis, viral hepatitis or autoimmune liver disease.Familial renal glycosuria.History of seizures or unexplained syncope.Pregnancy.Recent major change in body weight (>3 kg loss or gain in preceding month).BMI <20 kg/m^2^.History of malignancy.Presence of any other medical condition that would, in the opinion of the investigator, preclude safe participation in the study.Alcohol consumption in excess of daily recommended limits (14 units/week women, 21 units/week men).Any history of internal metal, pacemakers or ferromagnetic metallic implants intraocular foreign bodies or cerebral aneurysm clips (exclusion from MR scanning).Physical and laboratory test findings
ALT>3×upper limit of normal (ULN).AST>3×ULN.Bilirubin>2×ULN.Haemoglobin≤10.5 g/dL (≤105 g/L) for men; haemoglobin≤9.5 g/dL (≤95 g/L) for women.eGFR<60 mL/min.Unexplained haematuria.Weight>150 kg (due to limitations of MRI scanner).Allergies and adverse drug reactions
Any history of any serious hypersensitivity reaction to dapagliflozin or SGLT-2 inhibitor.Any allergy or intolerance to any of the study foods.Sex and reproductive status
WOCBP (woman of childbearing potential) who are unwilling or unable to use an acceptable method to avoid pregnancy for the study duration plus 8 weeks.Women who are pregnant or breastfeeding.Sexually active fertile men not using effective birth control if their partners are WOCBP.Prohibited treatments and/or therapies
Diabetes treated with pioglitazone, GLP-1 analogues or insulin.Use of other weight loss medication or any drug that might affect body weight or appetite (including antidepressants, antipsychotics, corticosteroids).Patients who are already receiving dapagliflozin or another SGLT inhibitor.Patients who have participated in a SGLT2 clinical trial within the past 30 days.Patients who are currently receiving a loop diuretic.Other exclusion criteria
Prisoners or participants who are involuntarily incarcerated.Participants who are compulsorily detained for treatment of either a psychiatric or physical (eg, infectious disease) illness.

